### Hypotheses

*Primary hypothesis*: Implementation of the Let’s CHAT Dementia model of care and health system changes will result in an increase in documentation of cognitive assessment and management for dementia and CIND in the clinic population aged 50 and over.

*Secondary hypothesis*: Compared with usual care, implementation of the Let’s CHAT Dementia model of care will: a) improve carers’ quality of life; and b) improve health outcomes and quality of life of those with CIND and dementia and help with health economic evaluation.

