#### Individuals

Patients identified through the medical record audit as having documentation of suspected or confirmed dementia or cognitive impairment and their carers will be approached to participate in a comprehensive geriatric assessment (CGA). The individual assessments will serve the dual purpose of enabling the measurement of individual outcomes across the course of the study and feeding back care recommendations for patient management from project geriatricians to ACCHSs and assisting with health economic evaluation. For each person suspected/identified as having cognitive impairment or dementia two case controls matched for age and gender will also participate in the CGA wing of the study. A known staff member or clinician from the ACCHS will make contact, inform the potential participants about the study and introduce a research staff member. The research staff member will then speak with the person/family to provide further information on the study and invite the person to participate.

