#### Sample size

Previous work in the Kimberley (confirmed by work in NSW) found that in Aboriginal and Torres Strait Islander communities, based on community screening, the true prevalence of dementia in people aged 45 years and over was approximately 10%, and the prevalence for cognitive impairment without dementia was also approximately 10% [5, 45]. Hence, the true prevalence of dementia or cognitive impairment in the relevant population is 20%. In the Kimberley, only 38% of those with dementia and only 3% of those with cognitive impairment had been diagnosed by primary health care practitioners. Moreover, the fraction of dementia cases identified by primary care in this work was likely to be higher than in standard practice as many of those with diagnosed dementia had been identified as part of previous research, with primary care practitioners subsequently notified. Therefore, we assume that no more than 15% of individuals with cognitive impairment or dementia are currently identified by primary health practitioners. The initial prevalence based on detection in primary care will be 15% of 20%, i.e. 3%. At a minimum, the study intervention should enable practitioners to identify at least half (50%) of the primary care patients with dementia or cognitive impairment. This would increase the prevalence based on detection in primary care to 50% of 20%, i.e. 10%. If an intraclass correlation of 0.01 and an average cluster size of 50 individuals is assumed, then the design effect will be 1.49. If the study was an individually randomised trial and we wished to detect an increase in the identification of cognitive impairment and dementia from 3 to 10% then the sample size would need to be at least 388 people (α = 0.05, power = 0.8). Therefore, the sample size required for this cluster randomised study will be 578 (388 × 1.49). Allowing for 10% drop-outs we plan to recruit 12 clusters of at least 55 people each, a total sample size of at least 660 individuals. Secondary outcomes compare the effect of earlier detection on scales of depression and stress and this sample size also has adequate power for these scales. We expect approximately 18 cases to be detected in the control period and 60 in the intervention period. The average cluster size will be 6.5 and assuming an ICC of 0.01, the design effect will be 1.055. Thus, our effective number of control cases will be 17 (18/1.055) and intervention cases 57 (60/1.055). Based on the variation found on the longitudinal data of carer strain in the Kimberley, our proposed study will provide over 80% power to find any clinically important effects.

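### The secondary outcomes are sized on cases detected before versus after crossover, but the programme changes who is detected, so the groups can differ with no true benefit

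*Protocol article*

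**What the plan says.** The Hypotheses section states the secondary hypothesis as a comparison with usual care: the programme is to improve carers' quality of life and to "improve health outcomes and quality of life of those with CIND and dementia". The Outcomes section says that the secondary outcomes are measured with two quality-of-life tools in the CGA.

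Entry to the CGA is set out under Individuals. Those approached are "Patients identified through the medical record audit as having documentation of suspected or confirmed dementia or cognitive impairment and their carers", together with two controls per case matched on age and gender. Under Outcomes, documentation of dementia or CIND is the primary outcome. The Introduction gives the programme's purpose as timely detection, with emphasis on early stages.

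The Sample size section describes the secondary outcomes as comparing the effect of earlier detection on depression and stress scales. It then gives the split: "We expect approximately 18 cases to be detected in the control period and 60 in the intervention period". It applies a design effect of 1.055, arrives at 17 and 57 effective cases, and claims more than 80% power, citing variation in carer strain. The same section reports that under usual care in the Kimberley "only 38% of those with dementia and only 3% of those with cognitive impairment had been diagnosed by primary health care practitioners".

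The Analysis section specifies generalised linear mixed models with random effects for cluster and time. It does not address differences between the groups of detected cases. The Data collection timetable schedules participant and carer assessments at baseline and 12-monthly.

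**The concern.** The stepped-wedge randomisation makes services comparable before and after crossover, up to time effects. It does not do so for subgroups whose membership the intervention determines. Being a detected case happens after randomisation, and the programme is expected to raise the count from 18 to 60. The additional cases are the ones that usual care misses. By the programme's own aim these are likely to be earlier or milder, with more CIND among them.

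If milder cases score better on mood, stress, quality of life or carer burden, the intervention-period group will score better on average even if nobody's condition or care has changed. Earlier detection within each diagnosis (lead time) would act in the same direction. Neither the matching on age and gender nor a random effect for service or time removes a difference in severity between the two groups of detected cases.

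At stake is the reading of the secondary hypothesis: a favourable between-period difference could not be told apart from a change in case mix. The primary outcome is unaffected, because it counts documentation in the audited population.

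**Working it through.** **1. Reproducing the plan's figures (Sample size section).**
- Primary: 3% versus 10%, two-sided α = 0.05, power 0.80, pooled variance, no continuity correction gives 194 per arm, 388 in total, as stated. Sidedness is not stated; the two-sided form reproduces the figure. Then 388 × 1.49 = 578.
- Secondary: with 12 × 50 = 600 people, 3% × 600 = 18 and 10% × 600 = 60. The average is (18 + 60)/12 = 6.5 cases per cluster. The design effect is 1 + 5.5 × 0.01 = 1.055. Effective numbers are 18/1.055 = 17.1 and 60/1.055 = 56.9.

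All stated figures reproduce. The secondary calculation therefore does set control-period detections against intervention-period detections.

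**2. Case mix under usual care.** The plan takes 10% dementia and 10% CIND as true prevalence.
- At 38% and 3% detection: 0.38 × 10 = 3.8 and 0.03 × 10 = 0.3 per 100 people. The dementia share of detected cases is 3.8/4.1 = 93%.
- These rates give 4.1% detected, above the 3% that the plan adopts. Keeping CIND detection at 3% and setting overall detection to 15% implies 27% detection of dementia: 2.7/(2.7 + 0.3) = 90%.

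The control-period share is thus about 90–93%.

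**3. Case mix under the programme.** The plan fixes only the total, 50% of all cases. With equal prevalences, let D be the proportion of dementia detected. CIND detection is then 1 − D, and the dementia share of detected cases equals D. The documents do not give D, so it is varied here.

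| Dementia detected (D, assumed) | CIND detected | Fall in dementia share |
|---|---|---|
| 38% | 62% | 0.52–0.55 |
| 50% | 50% | 0.40–0.43 |
| 70% | 30% | 0.20–0.23 |
| 90% | 10% | 0.00–0.03 |
| 100% | 0% | −0.10 to −0.07 |

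Reaching 50% overall with the mix unchanged would need about 90–93% of dementia but only 7–10% of CIND to be found. That sits poorly with an aim of early detection, so a shift towards CIND is likely, though not certain.

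**4. Spurious difference with zero true effect.** This is the fall in dementia share × the dementia–CIND gap in SD units. The documents give no scores by diagnosis, so the gap is an assumption. At D = 50%:
- gap 0.3 SD: 0.12–0.13 SD
- gap 0.5 SD: 0.20–0.21 SD
- gap 0.8 SD: 0.32–0.34 SD

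**5. Consequence for a test.** With 17 versus 57 effective cases, the standard error is √(1/17 + 1/57) = 0.276 SD. A two-sided 5% test would then reject in about 7%, 11–12% and 21–24% of trials for the three gaps, with no benefit. For scale, the difference detectable with 80% power is (1.960 + 0.842) × 0.276 = 0.77 SD.

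**The case against.** The strongest reply is that the 18 and 60 come from a power calculation, not an analysis specification, and that the calculation concerns depression, stress and carer strain, not quality of life. The CGA is described as following individual outcomes over the study, assessments repeat every 12 months, and the carer-strain variation comes from longitudinal data. All of this is compatible with a repeated-measures analysis, whose detail may properly sit in a statistical analysis plan.

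Part of this stands. Quality of life is connected to the contrast only by reading Hypotheses, Individuals and Outcomes together. But the article does state the contrast on which its power claim depends, and that contrast counts people by the period in which they were detected. The repeat assessments make a better analysis possible; the calculation does not use them.

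Three stronger readings are tempting and are not supported:
- A reader might infer that quality of life will look better under the programme even with no benefit. That needs the programme's dementia/CIND mix and the score difference between the two diagnoses. The documents give neither, and the shift disappears or slightly reverses at high dementia detection.
- A reader might take 90–93% as the dementia share of control-period CGA cases. The underlying rates are for diagnosis by practitioners. CGA entry also admits suspected impairment, a broader gate, so the actual mix may differ.
- A reader might infer that the cost-utility result is biased. The Health economic analysis section names EQ-5D but does not say whose scores are compared, and matched controls also complete the CGA.

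**Conclusion.** The concern holds in a limited form. The secondary comparison that the plan uses for its power claim is between groups selected after randomisation by the very thing the intervention changes, and the article states no safeguard. A difference between periods can therefore arise without benefit, probably in the programme's favour.

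Its size cannot be settled from the documents. At equal 50% detection of both diagnoses (assumption) it is 0.40–0.43 times the dementia–CIND gap, or 0.12–0.34 SD for assumed gaps of 0.3–0.8 SD. It is larger if the gain is mainly in CIND, and nil or slightly reversed if about 90% or more of dementia is found. Lead time within each diagnosis is not included in these figures. The weakness affects interpretation of the secondary outcomes only.

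**What to change.** 1. Label the comparison of cases detected in the control period with cases detected in the intervention period as descriptive. Report it separately for dementia and CIND, and do not present it as the programme's effect on quality of life, mood, stress or carer outcomes.
2. Base any effect claim on within-person change in clients and carers whose first CGA precedes their service's crossover, using the baseline and 12-monthly assessments already scheduled.
3. Withdraw or restate the claim of more than 80% power for the secondary outcomes, since it rests on the 18 versus 60 split.
4. If the cost-utility analysis uses EQ-5D from detected cases by period, state this and apply the same caution.

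No new data collection is needed, but the cost is more than wording. On the plan's figures the pre-crossover set is about 18 cases, or 18/12 = 1.5 per service. Assessments are 12-monthly while services cross over at six-monthly steps, so separating time from exposure will be difficult and intervals will be wide. The matched controls do not enlarge the set of people with CIND or dementia whom the hypothesis concerns. The question also changes: this analysis addresses the effect of the programme on people already identified, and leaves the effect of earlier detection itself unestimated.

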### Outcomes

The *primary outcome* is new documentation of dementia or CIND within healthcare records. This includes: (i) evidence of cognitive screening, and/or (ii) documentation of inquiry into cognitive health (e.g. asking questions regarding memory; obtaining informant report regarding cognition; (iii) laboratory or imaging investigations specifically requested for assessment of dementia. The data informing the primary outcome measure will be collected during regular audit cycles (detailed below), both prior to and during the project implementation phase.

*Secondary outcomes* are focused on improved health and well-being of older Aboriginal and Torres Strait Islander peoples with dementia, their carers and families. This will be measured through two validated quality of life tools in the CGA (refer below).

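### The claim of over 80% power for any clinically important secondary effect is unsupported, and it refers to scales other than the defined quality-of-life outcomes

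*Protocol article*

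**What the plan says.** The last part of the Sample size section turns to the secondary outcomes. It says "Secondary outcomes compare the effect of earlier detection on scales of depression and stress" and calls the sample adequate for those scales. It expects about 18 detected cases in the control period and 60 in the intervention period, with an average of 6.5 cases per cluster, an intraclass correlation (ICC) of 0.01 and a design effect of 1.055. It then states "Thus, our effective number of control cases will be 17 (18/1.055) and intervention cases 57 (60/1.055)". Citing the variation in longitudinal carer-strain data from the Kimberley, it concludes that "our proposed study will provide over 80% power to find any clinically important effects".

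The Outcomes section describes the secondary outcomes as the health and well-being of older people with dementia, their carers and families, and adds: "This will be measured through two validated quality of life tools in the CGA". The Abstract and the aims section also name quality of life, for older people and for carers. The Hypotheses section adds health outcomes in general terms but names no depression or stress scale. Appendix 1 lists depression, stress and carer-burden instruments among the many tools of the comprehensive geriatric assessment (CGA). It does not designate them as secondary outcomes.

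**The concern.** Two things look wrong.

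- **Outcomes.** Three constructs are in play: depression and stress (named as the secondary outcomes), carer strain (the source of the variation) and quality of life (the outcome as defined). The only power statement for the secondary outcomes concerns the first two, so the reader is told nothing about the third.
- **Size of the claim.** Effective groups of 17 and 57 are small and unequal. A promise of more than 80% power for any important effect, across several scales, needs every important effect to be large relative to its SD. The article shows nothing to that effect.

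At stake is how a null secondary result is read. If quality of life shows no significant change, the stated power invites the conclusion that no important benefit exists, when the study may have had less than an even chance of detecting a moderate one.

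**Working it through.** **Inputs, all from the Sample size section:** 18 and 60 expected cases; 6.5 cases per cluster; ICC 0.01. Alpha is not restated for the secondary outcomes. I take two-sided 5%, because a two-sided test reproduces the primary calculation (last step below).

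**The plan's intermediate figures reproduce.**

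- Cases per cluster: (18 + 60)/12 = 6.5.
- Design effect: 1 + (6.5 − 1) × 0.01 = 1.055.
- Effective cases: 18/1.055 = 17.1 and 60/1.055 = 56.9.

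**The 80% cannot be reproduced,** because it needs an SD and a target difference and the article gives neither. What 17 and 57 can detect is calculable in SD units.

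- Standard error of a difference in means: √(1/17 + 1/57) = 0.276 SD.
- Difference with 80% power, normal approximation: (1.960 + 0.842) × 0.276 = 0.77 SD.
- The same by noncentral t on 72 degrees of freedom: 0.785 SD.

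Power of the unadjusted two-sided 5% t-test at 17 versus 57 (the true differences are my benchmarks, not figures from the article):

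| True difference | Power |
|---|---|
| 0.3 SD | 19% |
| 0.4 SD | 30% |
| 0.5 SD | 43% |
| 0.6 SD | 57% |
| 0.7 SD | 71% |
| 0.8 SD | 82% |

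**More favourable variants at 80% power.**

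- One-sided 5% (normal approximation): 0.69 SD.
- Raw counts of 18 and 60, ignoring clustering: 0.76 SD.
- Adjustment for a baseline value with correlation ρ, which multiplies the SD by √(1 − ρ²): 0.785 × 0.866 = 0.68 SD at ρ = 0.5; 0.785 × 0.714 = 0.56 SD at ρ = 0.7; 0.785 × 0.6 = 0.47 SD at ρ = 0.8. These correlations are assumed.
- Correlation needed for 80% power at 0.5 SD: √(1 − (0.5/0.785)²) = 0.77. At 0.3 SD it is about 0.92.

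**What the 17 and 57 leave out.** The counts 18 and 60 are 3% and 10% of the same 600 people (12 × 50). No allowance is shown for detected cases or carers who do not take part in the CGA, or for adjusting for calendar time in the stepped-wedge analysis. I do not quantify either.

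**The primary calculation is untouched.** The article says "the sample size would need to be at least 388 people (α = 0.05, power = 0.8)" for a rise from 3% to 10%. A two-sided test without continuity correction gives 194 per arm, or 388. Then 1 + 49 × 0.01 = 1.49; 388 × 1.49 = 578; 578/0.9 = 643 after rounding up, which 12 × 55 = 660 covers.

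**The case against.** The strongest defence is that nothing here proves the 80% wrong. The claim is false only if some clinically important effect lies below the detectable difference, and the article sets no such threshold. Its variance source is described as longitudinal, the CGA and carer outcomes are collected at baseline and 12-monthly, and the Analysis section plans mixed models, so an unadjusted comparison of single measurements may be too pessimistic. A condensed article may also leave the SD and the target difference to the full protocol.

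Much of this stands. A reader might infer that the power claim has been shown to fail, or that its arithmetic is wrong. The documents support neither: every printed figure reproduces, and 0.5 SD is my benchmark. The missing SD alone would not be a finding either. What the defence does not rescue is the word any. Even at an assumed correlation of 0.8 the detectable difference is about 0.47 SD, and the article does not say how far baseline adjustment applies to newly detected cases. Variation in carer strain cannot settle the matter for several different scales.

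On the outcomes, it is fair to say that the Hypotheses section mentions health outcomes and that depression, stress and carer-burden tools are in the CGA. But the Outcomes section says how the secondary outcomes will be measured, and those tools are not what it names.

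Two further inferences should be resisted. One is that the economic evaluation depends on this claim: that section uses the EQ-5D but does not refer to the power statement, and the Sample size section does not mention the economic analysis. The other is that incomplete uptake lowers power by a known amount. The article gives no uptake rate. The counts of 18 and 60 are based on 600 rather than the 660 to be recruited, and the CGA invites suspected as well as confirmed cases, so the number who will take part is not established.

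**Conclusion.** The statement is wrong as written, in two respects. The Sample size section attaches its secondary power claim to depression, stress and carer strain, while the Outcomes section defines quality-of-life measures; that is an inconsistency within the article. The claim of over 80% power for any clinically important effect is also unsupported. On 17 versus 57 effective cases it holds only if no effect smaller than about 0.78 SD is important (two-sided 5%, unadjusted), or smaller than about 0.68 to 0.47 SD under assumed baseline correlations of 0.5 to 0.8. Power at an assumed 0.5 SD is about 43% unadjusted. The claim is not strictly disproved, since no SD, important difference or correlation is stated, but it is untenable as a blanket assurance covering moderate effects. The primary outcome and the sample size of 660 are not affected.

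**What to change.** In the Sample size section:

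- Delete the assertion of power for any clinically important effect and the assertion of adequate power for the depression and stress scales.
- State the detectable difference from 17 and 57 effective cases, with test, alpha and adjustment: about 0.8 SD at 80% power, two-sided 5%, unadjusted. If baseline adjustment is relied on, give the assumed correlation and its source. State the participation assumed and whether time adjustment is allowed for.
- If an 80% figure is kept for a named scale, print the SD and the important difference behind it.
- Reconcile the section with the Outcomes section, so that the power statement refers to the quality-of-life measures defined there. If depression, stress or carer strain are meant to be secondary outcomes, the Outcomes section must say so.

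The cost is wording and a less favourable stated figure. Recruitment, data collection and the primary analysis do not change.

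### The claim of over 80% power for any clinically important secondary effect is not supported by the plan's own 17 versus 57 effective cases

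*Protocol article*

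**What the plan says.** All of the power reasoning is in the Sample size section of the protocol article.

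- **Scales covered.** "Secondary outcomes compare the effect of earlier detection on scales of depression and stress and this sample size also has adequate power for these scales".
- **Expected cases.** "We expect approximately 18 cases to be detected in the control period and 60 in the intervention period".
- **Clustering.** "The average cluster size will be 6.5 and assuming an ICC of 0.01, the design effect will be 1.055". From this the section obtains 17 effective control cases and 57 effective intervention cases.
- **Conclusion.** "Based on the variation found on the longitudinal data of carer strain in the Kimberley", it states that "our proposed study will provide over 80% power to find any clinically important effects".

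The section gives no SD, target difference or smallest important difference for carer strain, depression, stress or quality of life. The Outcomes section says the secondary outcomes are measured by two quality-of-life tools, and the secondary hypothesis names carers' quality of life. No variation is cited for any of these.

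**The concern.** The word 'any' makes the claim universal: it must hold for the smallest difference that matters on every scale it covers. Seventeen effective cases in one group is a small number for such a claim, and the section offers no difference or SD that would make it good. The basis cited (carer strain) is also not the set of scales the section says are adequately powered (depression and stress).

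These outcomes carry the secondary hypotheses. If the power statement stands, a non-significant result could be taken as evidence against any worthwhile benefit to carers or clients, when the data could not bear that reading.

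**Working it through.** **1. The plan's own figures.** The primary calculation gives "α = 0.05, power = 0.8" without saying whether the test is one- or two-sided. The two-sided formula for 3% versus 10% (mean 6.5%) is

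n per group = [1.960 × √(2 × 0.065 × 0.935) + 0.842 × √(0.03 × 0.97 + 0.10 × 0.90)]² / 0.07² ≈ 193.5, rounded up to 194.

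Twice 194 is 388, the stated figure, so two-sided 5% is taken as the plan's convention.

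The secondary figures also reproduce:
- average cluster size: (18 + 60)/12 = 6.5
- design effect: 1 + (6.5 − 1) × 0.01 = 1.055
- effective cases: 18/1.055 = 17.06 and 60/1.055 = 56.87

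The claim of over 80% power can be neither reproduced nor refuted as a number, because no difference or SD is given.

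**2. What 17 versus 57 can detect.** Take the effective numbers as correct and compare two means, two-sided 5%, in SD units.

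- Standard error: √(1/17 + 1/57) = 0.2763 SD.
- Difference with 80% power, normal approximation: (1.960 + 0.842) × 0.2763 = 0.774 SD.
- The same by the non-central t distribution (72 degrees of freedom): 0.785 SD.

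| True difference (SD) | Power, t-test |
|---|---|
| 0.2 | 11% |
| 0.3 | 19% |
| 0.4 | 30% |
| 0.5 | 43% |
| 0.6 | 57% |
| 0.7 | 71% |
| 0.8 | 82% |

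The 95% confidence interval extends about 1.960 × 0.2763 = 0.54 SD either side of the estimate, so an observed difference of zero would leave differences of around half an SD in play.

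**3. Sensitivity to assumptions that the section does not state.**

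| Setting | Difference with 80% power (SD) | Power at 0.5 SD |
|---|---|---|
| 17 v 57, two-sided, t | 0.785 | 43% |
| 18 v 60 (no design effect), two-sided, t | 0.76 | 45% |
| 17 v 57, one-sided 5%, normal | 0.687 | 56.5% |
| 17 v 57, baseline correlation 0.5, normal | 0.67 | 55% |
| 17 v 57, baseline correlation 0.7, normal | 0.55 | 72% |

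The last two rows multiply 0.774 by √(1 − ρ²). Starting from 0.785, a correlation of 0.5 gives 0.785 × 0.866 = 0.68. A correlation of about 0.77 is needed for 80% power at 0.5 SD.

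**4. Dependence on the case counts.** The counts 18 and 60 are 3% and 10% of 600 (12 × 50), so the whole cohort is counted in both periods. If 600 were instead split into 300 per condition, the counts would be 9 and 30. Before any design effect, the detectable difference would then be 1.06 SD (normal) to 1.09 SD (t), with 25 to 26% power at 0.5 SD. This is shown only to mark that 0.78 SD is conditional on 18 and 60.

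**The case against.** A reader might infer from these figures that the claim is false, or that the section contains an arithmetic error. The document supports neither reading. Every figure that can be checked reproduces. To contradict the claim one would need the smallest important difference in SD units, which is not given. If that difference on the carer-strain scale were about 0.78 SD or more, the sentence would be true for this comparison. The 0.5 SD benchmark is an assumption of this review; the protocol nowhere calls it important.

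The simple t-test is also not the planned analysis. The Analysis section specifies mixed models with random cluster and time effects. Client and carer assessments are repeated every 12 months, and the cited carer-strain data are longitudinal. Using baseline values could lower the detectable difference, as shown. Adjusting for time in a stepped-wedge design would be expected to raise it. So 0.78 SD is not established as the study's detectable difference in either direction.

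Finally, an article may leave the SD and target difference of a secondary outcome to the full protocol, and their absence alone would not be a finding.

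These points limit the conclusion but do not remove it. The article goes beyond omitting detail: it makes an affirmative, unqualified claim next to case numbers that do not carry it. The rescue by baseline adjustment needs a high correlation that is not stated, and the model described mentions no baseline covariate. Nor does variation in carer strain support a claim about depression and stress scales.

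**Conclusion.** The two power statements are unsupported as written. On the plan's own effective numbers, an unadjusted two-sided 5% comparison reaches 80% power only at about 0.78 SD (about 0.68 SD with an assumed baseline correlation of 0.5). It has about 43% power if 0.5 SD is taken as important. The claim could stand only if nothing below roughly 0.7 to 0.8 SD mattered on any of the scales, or if an unstated and strong gain from repeated measures applied.

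The conclusion rests on 17 and 57 as given, a two-sided 5% level carried over from the primary calculation, and no allowance for time adjustment. It does not touch the primary outcome or the planned 660 participants. Nor does the document say that a null secondary result will be read as excluding benefit; that is a risk created by the wording, not a stated intention.

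**What to change.** In the Sample size section, delete the claim about any clinically important effects and the claim of adequate power for the depression and stress scales. In their place, name each secondary scale and state its detectable difference, with the SD used and its source. Until that is worked out under the planned model, wording such as this would be accurate:

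> Conditional on the assumed 18 and 60 cases (17 and 57 after the design effect), an unadjusted two-sided 5% comparison has 80% power for a difference of roughly 0.78 SD. This makes no allowance for time adjustment under the planned mixed model. Secondary outcomes will be reported as estimates with 95% confidence intervals, and a non-significant result will not be read as no effect.

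The 0.78 SD should carry those conditions and should not be presented as the study's established detectable difference. The cost is a less favourable power statement. No extra participants and no change to conduct are needed.
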